### Volunteer recruitment

Posters will be disseminated at the hospital to recruit participants. During their appointment at the Department of Gastroenterology in the First Affiliated Hospital of Nanchang University, volunteers who are interested in the study will undergo preliminary evaluations based on the inclusion and exclusion criteria. Additionally, the investigator will explain the purpose, process, and potential benefits and risks of this study, and the volunteers may choose to participate by signing the informed consent form. Next, the volunteers will undergo further screening to determine their eligibility. Eligible participants will receive the study intervention and follow-up. The following steps describe the formal intervention and follow-ups (Table 1).

**Table 1 Tab1:** Study and follow-up schedule

Item^1,10^		Screening	Baseline	Initial treatment		Maintenance treatment
		Visit 0	Visit 1	Visit 2	Visit 3	Visit 4
		Days −3 to 0	Day 0	Week 4	Week 8	Week 12
Basic demographics		X				
Vital signs, physical examination		X				
Allergies, medical history^2^, medication history^3^, surgical history^4^		X				
Smoking and drinking		X				
Gastroscopy		X^5^				X^6^
Abdominal ultrasound B^7^		X				
Serum human chorionic gonadotropin (hCG)		X				
ECG		X				X
Blood test, urine analysis, stool test (including occult blood)		X				X
Liver/kidney function^8^		X				X
Signed informed consent		X				
Inclusion/exclusion criteria verification			X			
Primary outcome measure	GM^11^ (metagenomics)	X		X	X	X
Secondary outcome measures	RDQ	X	X	X	X	X
	GSRS		X	X	X	X
	Faecal metabolomics^11^	X		X	X	X
	BMI ^9^		X	X	X	X
	LA grade	X				X
Safety measures	AEs			X	X	X
	SAEs			X	X	X
Compliance verification			X	X	X	
Concomitant medications		X	X	X	X	

^1^Visit window: 0 days for visit 1; ± 2 days for visits 2, 3, and 4

^2^Medical history: current and past illnesses, including peptic ulcer, gastritis, oesophagitis, cardiovascular and cerebrovascular diseases, cancer, and mental illness

^3^Medication history: PPI, histamine H2 antagonists, antibiotics, probiotics, prokinetics, gastric mucosal protectors, and other drugs for gastro-oesophageal reflux (including herbs)

^4^Surgical history: gastrointestinal surgeries, including gastro-oesophageal and duodenal surgeries

^5^Performance of gastroscopy in domestic tertiary or higher hospitals in the past 3 months

^6^Gastroscopy at visit 4, LA grades at visit 0 and visit 4 referring to patients with oesophagitis (LA-A, LA-B or LA-C)

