### Secondary outcome

RDQ score: The RDQ (see Additional file 1: Appendix 5) includes 4 symptoms: heartburn, acid reflux, regurgitation, and noncardiac chest pain. Each symptom is rated on a 0–5 scale based on its frequency and severity in the last week. The total score is 40, and a higher score is associated with more severe symptoms. RDQ ≥ 12 indicates GERD [18, 21]. The RDQ will be used to evaluate reflux-related symptom scores on day 0 (week 0), day 28 (week 4), day 56 (week 8), and day 84 (week 12).GSRS score: The GSRS (see Additional file 1: Appendix 6) is a self-rating scale that includes 15 items in 5 subscales (abdominal pain, acid reflux, dyspepsia, constipation, and diarrhoea). Each item is rated on a Likert scale ranging from 0–3 (none, mild, moderate, mild) based on the severity of symptoms in the last week. The total score is 45, and a higher score is associated with more severe symptoms [22–24]. The GSRS will be used to evaluate gastrointestinal disease symptom scores on day 0 (week 0), day 28 (week 4), day 56 (week 8), and day 84 (week 12).Faecal metabolome (FM): Based on the faeces, FM from day 0 (week 0), day 28 (week 4), day 56 (week 8), and day 84 (week 12) will be evaluated. Stool samples will be extracted using the protein precipitation method, and the supernatant will be transferred to sample vials for mass spectrometry combined with liquid chromatography (LC–MS/MS) analysis. The original data will be subjected to peak alignment, retention time correction, and peak area extraction through the XCMS-Plus program. The structure of metabolites will be identified by accurate mass matching (< 5 ppm) and two-level spectrum matching, and the METLIN database will be retrieved. Missing values > 50% in the group will be deleted, and the data will be normalized. Multidimensional statistical analysis will then be carried out, including unsupervised principal component analysis (PCA), supervised partial least squares discriminant analysis (PLS-DA) and potential differential metabolite analysis. Metabonomic analysis could further identify the potential differential metabolites of probiotics in the treatment of GERD, and correlation analysis between the gut microbiota and metabolites could be performed.Change in the Los Angeles (LA) grade of oesophagitis: According to gastroscopy, the change in the LA grade of oesophagitis will be evaluated.Body mass index (BMI): BMI = weight (kg)/height (m)^2^. BMI will be measured in the morning using the same weight and height scales at each visit. Participants will be instructed to wear light clothing and take off their shoes (standing barefoot or wearing socks no thicker than 0.1 cm) during the weight and height measurements.AE rate: all the AEs collected as described below will be used to calculate the AE rate in each group.Treatment compliance will be monitored as described in the “Volunteer compliance monitoring” section. Although efforts have been made to promote treatment compliance, there may still be differences between the two groups due to AEs.

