
### Safety evaluation

AEs will be evaluated with blood tests, urine analysis, and stool tests (> 2 × ULN or < 2 × LLN); liver tests (ALT, AST, total bilirubin); renal tests (Scr, blood urea nitrogen); and ECG. AEs may be related or unrelated to the study interventions.At each visit, the patients will be asked about any AEs with nondirective questions. Patients may also voluntarily report AEs.Severe adverse events (SAEs) are events that occur after the study interventions are provided and result in hospitalization, prolonged hospitalization, disability, impaired ability to work, threats to the patient’s life, or death. All SAEs must be reported to the Ethics Committee of the hospital and the sponsor. Participants with SAEs will discontinue the interventions.Treatment-related AEs must meet the following criteria: a reasonable temporal/causal relationship with the treatment; side effects unrelated to comorbidities or concomitant medications; improvement or resolution of AE symptoms after treatment discontinuation; and causality can be explained with a pharmacological, biological, or phenomenological mechanism.

Drug-related AEs: possible adverse reactions experienced while taking rabeprazole include allergies (rash, itching, urticaria), abnormal blood test results, abnormal biochemical parameters, high blood pressure, gastrointestinal symptoms (constipation, diarrhoea, abdominal distension, nausea, lower abdominal pain, bitter taste in the mouth), headache, dizziness, palpitations, fever, fatigue, hypoesthesia, dry mouth, blurred vision, and vomiting. Possible serious adverse reactions include shock, interstitial nephritis, liver dysfunction, jaundice, anaemia, and hyponatremia. Possible adverse reactions to probiotic ingestion include diarrhoea, constipation, and weight loss.

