### Sample size

This is a superiority study. Based on pilot case observations and expert feedback, the major indicator Chao1 index (α-diversity) at week 12 is expected to differ by 145 between the two groups, with a standard deviation of 230 [25]. Assuming *α* = 0.025 and *β* = 0.20, we calculated that the sample size should be at least 47.9 in each group [26]. If the lost-to-follow-up rate is no more than 20%, the sample size should be at least 57.5 in each group. Moreover, Shannon’s index (α-diversity) of the primary measure at week 12 is expected to differ by 0.9 between the two groups, with a standard deviation of 0.8. Thus, the sample size should be at least 15.0 in each group. If the lost-to-follow-up rate is no greater than 20%, the sample size should be at least 18.0 in each group. The larger value (57.5) is used as the calculated sample size. Based on the above assumptions and our budget, we will recruit a total of 120 participants for this study, with 60 participants in each group.

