### Statistical analysis

First, the intention-to-treat (ITT) analysis will be conducted between the two groups, including all the intended participants who do or do not complete the follow-up. Then, per-protocol (PP) analysis will be conducted in the four-subgroup datasets according to compliance (100%, ≥ 80%, 60–80%, and < 60%) to validate the robustness of the results. The datasets will be analysed as described below.

With a randomized block design, the nonparametric rank sum test and Friedman M test will be performed to analyse the difference in each outcome measure at each time point (see “Intervention Outcome Measures” for details) between the two groups, including the GM analysis, RDQ score, GSRS score, faecal metabolomics, and BMI. The significance level will be set to *P* = 0.05. Next, the paired Wilcoxon signed-rank test will be performed for pairwise intragroup comparisons to analyse the change trends for each outcome measure before, during, and after the probiotic intervention. The significance level will be set at *P* = 0.05/[k(k-1)/2], where k is the number of groups in the comparison. For analysis of the oesophagitis grade, the diagnosis of LA-B at baseline and LA-A at week 12 indicates that the patient's oesophagitis grade will have decreased by one level. If the grade is LA-C at baseline and LA-A at 12 weeks, the patient’s oesophagitis grade will have decreased by 2 levels. The number of oesophagitis grades reduced by 1 and 2 levels in each group will be calculated. Then, a chi-square (*χ*^2^) test will be performed. AE rates in the two groups will be compared by the *χ*^2^ test or Fisher’s exact probability test based on the occurrence frequency of AE, and the difference in treatment compliance will be also examined by the *χ*^2^ test.

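### The lower laboratory limit for adverse events, < 2 × LLN, lies above the lower limit of normal, so normal values count as adverse events and dilute the AE-rate comparison

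*Protocol article*

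**What the plan says.** The Safety evaluation section gives one numeric rule for laboratory AEs: "AEs will be evaluated with blood tests, urine analysis, and stool tests (> 2 × ULN or < 2 × LLN". The bracket follows the blood, urine and stool tests. The items listed next, "liver tests (ALT, AST, total bilirubin); renal tests (Scr, blood urea nitrogen); and ECG", carry no limit of their own. The section has two further sources of AEs: "At each visit, the patients will be asked about any AEs with nondirective questions" and "Patients may also voluntarily report AEs". SAEs are defined separately, by their consequences for the patient.

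Under Secondary outcome, the AE rate is defined in these terms: "all the AEs collected as described below will be used to calculate the AE rate in each group". In the Statistical analysis section, "AE rates in the two groups will be compared by the" chi-square test or Fisher's exact test.

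The schedule (Table 1, under Volunteer recruitment) lists "Blood test, urine analysis, stool test (including occult blood") at screening and at week 12 only, so each patient has one scheduled laboratory assessment after baseline. No other lower limit and no reference ranges appear in the article.

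**The concern.** Multiplying by 2 acts in opposite directions at the two ends of a reference range. At the upper end it moves the cut-off away from normal. At the lower end it moves the cut-off up into the normal range, or past the top of it. As written, a patient whose result is normal can be recorded as having an AE because of that result.

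This is a stated rule that is wrong, not a detail left to another document. It looks like a slip, but the intended limit cannot be recovered from the text, so a reader cannot silently correct it.

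The AE rate is how the safety of the probiotic is to be compared between arms. False AEs that arise equally in both arms push the two rates towards each other and towards 100%, which hides a real difference. The section also names anaemia among the possible serious reactions to rabeprazole. That is a low-side finding, and the low-side flag as written does not separate it from a normal result.

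**Working it through.** The article states no AE rate and no AE power, so it has no figure of its own to reproduce here.

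**Step 1. Position of the limit.** Let R = ULN/LLN with LLN > 0.
- 2 × LLN > LLN always, so the cut-off is never at or below the lower limit of normal.
- 2 × LLN > ULN exactly when R < 2. Every value in the normal range is then flagged.
- If R > 2, the cut-off falls inside the normal range and flags its lower part.
- A test with LLN = 0, or with no lower limit, flags nobody on the low side.

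This step is algebra and needs no assumption about the analytes. As an illustration with an assumed haemoglobin range of 130 to 175 g/L, R = 175/130 = 1.35. The cut-off is then 2 × 130 = 260 g/L, above the ULN.

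**Step 2. Share of healthy values flagged.** Assume LLN and ULN are the 2.5% and 97.5% points of a normal distribution. Scale so that LLN = 1 and ULN = R. Then mean = (1 + R)/2, SD = (R − 1)/3.92, and the share flagged = Φ((2 − mean)/SD).

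For R = 2.5: mean 1.75, SD 0.383, (2 − 1.75)/0.383 = 0.653, and Φ = 0.74.

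| Assumed R | Healthy values below 2 × LLN |
|---|---|
| 1.25 to 1.5 | practically 100% |
| 2 | 97.5% |
| 2.5 | 74% |
| 3 | 50% |
| 4 | 26% |
| 8 | 8% |

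Under the same model, a cut-off at LLN itself would flag 2.5% of healthy values per test, by construction.

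**Step 3. Effect on the comparison.** Input from the Sample size section: "we will recruit a total of 120 participants for this study, with 60 participants in each group". With the planned 20% loss, 60 × 0.8 = 48 remain. Assumptions:
- The AE rate is the share of patients with at least one AE.
- The test is two-sided at 0.05.
- A fraction f of patients in each arm is flagged by the faulty limit, independently of true AEs.
- The true rates are p1 and p2.

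The observed rates are a = f + (1 − f)p1 and b = f + (1 − f)p2. The observed difference is therefore (1 − f)(p2 − p1). With m = (a + b)/2,

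power = Φ{ [ |b − a| − 1.96 √(2m(1 − m)/n) ] / √([a(1 − a) + b(1 − b)]/n) }.

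For p1 = 10%, p2 = 30%, f = 0.5 and n = 60: a = 0.55, b = 0.65, m = 0.60. The two root terms are 0.0894 and 0.0890, so (0.10 − 1.96 × 0.0894)/0.0890 = −0.85 and power = 0.20.

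| f | 10% vs 30%, n = 60 | n = 48 | 20% vs 40%, n = 60 | n = 48 |
|---|---|---|---|---|
| 0 | 0.79 | 0.69 | 0.67 | 0.57 |
| 0.25 | 0.39 | 0.32 | 0.38 | 0.31 |
| 0.5 | 0.20 | 0.17 | 0.21 | 0.17 |
| 0.75 | 0.10 | 0.09 | 0.11 | 0.09 |
| 0.9 | 0.06 | 0.06 | 0.06 | 0.06 |
| 1 | no test possible | no test possible | no test possible | no test possible |

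At f = 1 both arms stand at 100%. This can occur only among patients who have the week-12 tests. If the denominator is all 60 and 12 have no week-12 test, f is at most 48/60 = 0.80.

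**The case against.** A reader might infer that the AE-rate comparison carries no information at all. The documents do not support that. It would need three things together: literal use of the limit, a panel containing an analyte with ULN/LLN of about 2 or less, and an AE rate counted as patients with any AE. The schedule names a blood test without listing analytes. The Secondary outcome section does not say whether patients or events are counted, or whether AEs are pooled or split by type. Symptoms found by questioning or reported voluntarily, SAEs, and liver, renal and ECG findings do not depend on this limit and could still be compared by type. This part of the objection stands, and it limits the conclusion to dilution, with saturation as the extreme case.

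It can also be said that nobody would apply the limit literally, because the section plainly means to capture abnormal results. That is plausible, but it does not supply the intended limit, and an edit check programmed from the text would apply the text.

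Two further inferences should be resisted. One is that genuinely low values are lost. Only the flag fails, and nothing suggests that the numeric results are discarded, so they can be reclassified. The other is that the rule leaves a gap for qualitative results such as occult blood. How to code those is detail that an article commonly leaves to the full protocol, and the text does not say that the bracket is the only route to an AE.

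**Conclusion.** The lower limit is wrong as written. That it lies above LLN for any positive LLN is certain and needs no assumption. Applied literally, it adds false AEs to both arms and dilutes the overall AE-rate comparison.

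The size of the effect depends on reference ranges and on a definition of the rate that the documents do not give. Over assumed ULN/LLN ratios from 1.25 to 8, between practically all and 8% of healthy values are flagged per test. For a patient-level any-AE rate with assumed true rates of 10% and 30% and 60 per arm, false flags in a quarter of patients roughly halve the power (0.79 to 0.39). Saturation at 100% follows only under the three conditions set out above, and only among patients tested at week 12.

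The primary outcome, the sample size, the randomisation and SAE reporting are unaffected.

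**What to change.** In the Safety evaluation section, replace < 2 × LLN with a lower limit that does not lie above LLN. The documents do not show which value was intended, so the sponsor's medical lead should set it, by analyte if needed, before AE coding and unblinding. Align the data-management edit check with the corrected text. If any laboratory AE has already been coded under the present limit, reclassify it from the numeric result.

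The cost is one line of text and one edit check, plus any recoding. No new tests, visits or patients are needed.

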### Volunteer compliance monitoring

For the initial treatment (weeks 1–8), the sample package will include rabeprazole and probiotics or rabeprazole and the probiotic placebo; for the maintenance treatment (weeks 9–12), the sample package will include probiotics or the probiotic placebo. After the start of the study, the volunteers will receive a sample package at each monthly visit (package 1 at visit 1, package 2 at visit 2, and package 3 at visit 3) and will be required to return the package at the next visit such that the remaining rabeprazole, probiotics, or probiotic placebo doses can be counted to calculate the compliance level based on the equation below. Compliance ≥ 80% indicates good compliance.

Compliance = [actual amount taken (packets)]/[(amount prescribed (packets)] × 100%

To improve compliance, the study staff will use push messages via a WeChat group established for this study to remind the volunteers to take the sample as scheduled. All volunteers who complete the follow-up will receive 100 yuan as compensation. Moreover, rabeprazole will be provided at no cost during the study.

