### Study intervention

The study treatment consists of two phases: an initial treatment period lasting 8 weeks (weeks 1–8) and a maintenance treatment period lasting 4 weeks (weeks 9–12). The patients will be randomized into two groups: a control group and an experimental group. The participants will not know the group to which they have been assigned.

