### Intervention strength and management

Rabeprazole: 10 mg/tablet, from Eisai China, Inc (Tokyo, Japan).

LiHuo Probiotics powder: LiHuo probiotics powder containing strains such as *Lactobacillus casei Zhang*, *Bifidobacterium lactis* V9, and *Lactobacillus plantarum* P9, 2 g/bar, each bar containing active probiotics (≥ 50 billion CFU), were obtained from Jiangzhong Pharmaceutical Company Limited (China). During the manufacturing of LiHuo probiotics powder, *Lactobacillus casei Zhang*, *Bifidobacterium lactis* V9, and *Lactobacillus plantarum* P9 were mixed according to concentrations of ≥ 5 billion CFU/g, ≥ 15 billion CFU/g, and ≥ 5 billion CFU/g, respectively.

Probiotic placebo powder: The ingredients are maltodextrin, orange powder, and maltitol, and there are no active ingredients. The appearance, packaging, storage method, and dosing are the same as those of the LiHuo probiotics from Jiangzhong Pharmaceutical Company Limited (China).

The rabeprazole, LiHuo probiotics, and probiotic placebo will be stored in a cool, dry place away from light. Refrigerated storage will retain the maximum activity of the product. Each patient will receive a sample that corresponds to his or her unique number. All remaining study drugs and empty packages will be collected at the end of the study.

The study will have three phases: the screening period, the initial treatment period, and the maintenance treatment period. The interventions in each phase are described below:Screening: No intervention.Initial treatment (weeks 1–8):Control group: rabeprazole and probiotic placebo. The samples will be distributed to the patients every month.Experimental group: rabeprazole and probiotics. The samples will be distributed to the patients every month.Rabeprazole dosage: 10 mg/tablet twice a day before meals;Dosage of probiotic placebo or LiHuo probiotics: 2 bars, once a day, with or without water (< 40 °C), after meals. Thus, the daily dosage of probiotics is more than 100 billion CUF. Participants who take antibiotics should wait 2 h before taking the probiotic placebo or LiHuo probiotics.Maintenance treatment (weeks 9–12):

Control group: probiotic placebo. The samples will be distributed to the patients every month.

Experimental group: probiotics. The samples will be distributed to the patients every month.

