### Data collection and collation

All study participants will be assigned a study ID. Electronic data will be stored in a secure password-protected database. All paper data collected will be stored at the site, and only the study team will have access to the data. The study results will be independently analysed at the end of the study. No interim analysis is planned. The GM and metabolomics data detected from stool samples will be analysed by the Key Laboratory of Dairy Biotechnology and Engineering, Ministry of Education. All records that contain names or other personal identifiers referring to a specific volunteer, such as ID number and informed consent forms, will be stored separately from the study records. The database will be password protected by the data management team (DMT).

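### Reminders through one study-wide WeChat group could let the two arms compare notes; one-to-one or one-way messages would remove this possible, minor threat to the blind

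*Protocol article*

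**What the plan says.** Under Volunteer compliance monitoring, the article states that "the study staff will use push messages via a WeChat group established for this study to remind the volunteers" to take their doses. The group is in the singular, the recipients are the volunteers, and nothing divides it by arm.

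The trial is double-blind. Under Study intervention: "The participants will not know the group to which they have been assigned". Under Randomization and blinding, packs carry unique numbers rather than arm names. Under Intervention strength and management, the placebo is described as follows: "The ingredients are maltodextrin, orange powder, and maltitol, and there are no active ingredients", and "The appearance, packaging, storage method, and dosing are the same as those of the LiHuo probiotics". The powder may be taken with or without water.

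Among the secondary outcomes, the GSRS "is a self-rating scale that includes 15 items in 5 subscales", and the RDQ scores the frequency and severity of four reflux symptoms over the past week. Under Safety evaluation, "the patients will be asked about any AEs with nondirective questions" at each visit and may also report events unprompted. Blood, urine, stool, liver and renal tests and the ECG are further sources of adverse events.

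**The concern.** A participant in a placebo-controlled trial normally has nothing to compare the product with. A channel shared by both arms can supply that comparison. If members can post, the obvious topics are what the powder is like and whether it is helping. Guesses about allocation could then form and spread.

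The outcomes that depend on the patient's own account are the ones exposed: GSRS, RDQ and patient-reported adverse events. A participant who believes they have the probiotic may rate symptoms more favourably, and one who believes they have placebo less so. Seeing others' complaints may also prompt adverse event reports, which would undercut the care taken to ask nondirective questions. Gastrointestinal symptoms are part of the study aim stated in the Abstract, so these outcomes matter even though they are secondary. Once participants have exchanged views, the effect cannot be undone in the analysis.

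**Working it through.** The plan states no figure on this point and no arithmetic settles it. The check is to set the relevant sections side by side.

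1. **Is there one channel for both arms?** Volunteer compliance monitoring describes a single group set up for the study, with no split by arm. One group for everyone is the natural reading.

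2. **Can members interact?** The article describes only staff sending reminders. It does not say whether members can post or see each other, whether the group is moderated, or whether volunteers are told not to discuss the product. Interaction is therefore an assumption, and the concern depends on it.

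3. **Could comparing the product reveal anything?** Intervention strength and management states matching on appearance, packaging, storage method and dosing. Taste and smell are not mentioned. The list is not said to be exhaustive, and nothing says that the products taste different. Comparison could be informative only through properties on which matching is not stated.

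4. **Could comparing symptoms reveal anything?** Both arms take the same rabeprazole in weeks 1–8, so relief of reflux is expected in both. Safety evaluation lists diarrhoea and constipation as possible reactions to rabeprazole and to probiotics alike, so bowel changes separate the arms poorly in that period. In weeks 9–12 only the powder remains, and a difference in symptoms would more readily be put down to it. Diarrhoea and constipation are also GSRS subscales, so what participants would talk about overlaps with what is measured. Such talk can prompt guesses; it does not disclose allocation.

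5. **Which outcomes are exposed?**

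| Outcome | Source | Depends on patient's belief? |
|---|---|---|
| Gut microbiome (primary) | Stool metagenomics | Not self-rated |
| GSRS | Patient's own rating | Yes |
| RDQ | Symptom report; mode of completion not stated | Yes, as reported symptoms |
| AEs by questioning or volunteered | Patient report | Yes |
| AEs by laboratory test or ECG | Measurement | Not self-rated |

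The exposed post-baseline assessments are those at weeks 4, 8 and 12.

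6. **How large could the bias be?** Suppose that believing oneself on probiotic lowers a score by *s*, and believing oneself on placebo raises it by *s*. Let *c* and *w* be the fractions guessing correctly and wrongly in each arm. The probiotic arm then shifts on average by −*s*(*c*₁ − *w*₁) and the placebo arm by +*s*(*c*₀ − *w*₀). The spurious difference is *s*[(*c*₁ − *w*₁) + (*c*₀ − *w*₀)]. It is zero when correct and wrong guesses balance. The document gives none of these quantities, so no size can be stated.

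**The case against.** The strongest reply is that the mechanism is not in the text. The article describes reminders from staff and nothing more. Group settings, moderation and instructions to volunteers are operational details that an article may leave to the full protocol or the participant information, neither of which is shown. This stands as a limit on the claim: silence about moderation is not a fault. The point rests instead on the delivery method that the article does state, a shared group, for which a safer equivalent exists.

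It is also fair that comparing notes might reveal little, given the stated matching, the numbered packs and the rabeprazole common to both arms in weeks 1–8. That lowers the risk without removing it.

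Three stronger readings are tempting, and the documents do not support them:

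- **That the blind is broken.** A reader might infer this from the shared group. No exchange between participants is described, no difference in taste or smell is stated, and guesses are not disclosure.
- **That confidentiality is breached.** A reader might cite the statement under Data collection and collation that "only the study team will have access to the data". That section governs access to study data and the storage of identifying records, not whether participants may know of each other. Randomization and blinding concerns concealment of the sequence and states no privacy aim.
- **That the primary result is compromised.** One could suppose that a participant who suspects placebo would take outside probiotics or skip sachets. Nothing in the article supports that chain.

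Nor should it be said that all 120 participants would share the channel throughout the same 84 days. Volunteers are numbered in order of participation and recruited around clinic appointments, so entry may be staggered.

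**Conclusion.** The point holds as a possible threat to the blind, of minor severity. It rests on two assumptions: that the single group contains volunteers of both arms, which is the natural reading, and that members can see and message each other, which the article neither states nor rules out. If both hold, participants could compare product and symptoms and form guesses about allocation. That could influence the GSRS, the RDQ and patient-reported adverse events. The primary outcome and the adverse events found by laboratory test or ECG are not self-rated. The documents supply no basis for a magnitude, and none is claimed.

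**What to change.** Keep the reminders and change how they are delivered. Send them one-to-one, or through a one-way broadcast in which participants can neither see nor message each other, with identical text and timing in both arms. Add a sentence asking participants not to discuss the product or their symptoms with other participants. If the group is already configured as one-way with members hidden from each other, stating so settles the delivery question.

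The cost is slightly more work for staff in sending the messages. The same reminder content can be kept.
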